### COVID-19 restrictions and adaptations

If COVID-19 restrictions are resumed, exercise physiologist led sessions using video conferencing may be used to replace some in-person supervised exercise sessions, using heart rate monitors, self-monitoring devices and resistance bands. Any remaining in-person intervention visits or outcome measurement sessions will be undertaken using personal protective equipment following clinical guidelines that are current at the time of practice.

### Sample size

In the DIRECT trial, remission was 46% at 1 year (vs 4% in control arm; OR 19.7).^9^ Even higher remission was observed over the shorter term in other studies.^57^ We initially allowed for a minimum 45% remission at 24 weeks in the intervention group and up to a 5% remission rate in the control group. Using a Fisher’s exact test with 90% power, a significance of 0.05, and a 1:1 ratio between intervention and control groups, we estimated needing 56 individuals to complete the trial (control=28, intervention n=28). Allowing for up to 30% drop-out, we planned to recruit 80 individuals in total (40 UK, 40 Canada) in our successful application for funding to the MRC and the Canadian Institutes of Health Research.

We subsequently obtained additional funding from the Canadian JR McConnell Foundation, and increased recruitment goals in Canada from 40 to 60 participants (40 UK, 60 Canada). With an overall sample size of 100 (40 UK, 60 Canada), if 70 (70%) complete the trial, we will have 90% power to detect a minimum 35% remission at 24 weeks in the intervention group and up to a 5% remission rate in the control group.

Retention of at least 35 participants in each arm (70 total) will provide over 80% power to detect a difference in mean peak early diastolic strain rate of 0.10/s difference, equivalent to the exercise effect in the DIASTOLIC trial (see BACKGROUND),^18^ assuming that the common SD is 0.144 as in the DIASTOLIC trial and using a two group t-test with a 5% two-sided significance level.

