### Statistical analyses

Our primary outcome measures the proportion of remission in the intervention arm relative to the control arm. We will apply intention-to-treat principles for the primary outcome, assuming that remission of diabetes did not occur if information is not available. Based on the DiRECT and DIADEM-I trials, we estimate that remission counts in the control arm could be less than 2. We will therefore use stratified Fisher’s exact test statistics (ie, stratification by country and by sex) if remission counts are low in the control arm but consider Pearson χ^2^ test, if appropriate. If numbers permit, logistic ORs with 95% CIs (exact method) will also be performed to further quantify the efficacy of intervention over the control group, after adjusting for factors used to stratify the randomisation (country, age or sex); we will not have missing values for these covariates. Subgroup analyses for the primary outcome will be performed by country, sex and the degree of weight loss (<5%, 5%–10%, 10%–15%, >15% as examined in the DiRECT trial,^9^ collapsing categories as needed, and by exercise adherence (<50%, >50% of supervised sessions attended). In a per-protocol analysis, we will restrict the intervention group to those who achieved at least 10% wt loss and adhered to at least two thirds of prescribed exercise sessions.

We will analyse dichotomous secondary outcomes (eg, diabetes remission at 12 weeks, hypertension remission at 12 and 24 weeks) as described for the primary outcome. We will analyse continuous key secondary outcomes (eg, left ventricular peak early diastolic strain rate, lean soft tissue mass) through linear regression or log-linear regression, as appropriate, with stratification by country and sex.

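### The stated 90% power (35% vs 5%, 70 completers) is not the power of the planned primary analysis: two-sided Fisher gives 87%, and about 83% or 97% under the ITT rule, depending on what the rates mean

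*Protocol article*

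**What the plan says.** The Sample size section gives two calculations for remission.

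- **Initial plan.** The assumed rates were 45% and 5% ("We initially allowed for a minimum 45% remission at 24 weeks in the intervention group and up to a 5% remission rate" for controls). The method was described as "Using a Fisher’s exact test with 90% power, a significance of 0.05, and a 1:1 ratio between intervention and control groups", and the result was that "we estimated needing 56 individuals to complete the trial (control=28, intervention n=28").
- **Expanded plan.** "With an overall sample size of 100 (40 UK, 60 Canada"), the section states that "if 70 (70%) complete the trial, we will have 90% power to detect a minimum 35% remission at 24 weeks in the intervention group". Control remission is again taken to be at most 5%. The power statement names no test.

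Sidedness is not given for either remission calculation. It is given only for the strain-rate calculation in the same section, "using a two group t-test with a 5% two-sided significance level".

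The Statistical analyses section makes the primary analysis intention to treat, "assuming that remission of diabetes did not occur if information is not available". It plans a stratified Fisher's exact test (country and sex) if control remissions are few, and it expects that they could number fewer than two. A Pearson chi-square test may be considered if appropriate.

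**The concern.** Two features of the 90% do not fit the rest of the plan.

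1. **Test.** Fisher's test is conservative at these sample sizes. A figure from a large-sample formula will overstate its power.
2. **Population.** The calculation sets the sample size to those who complete. The analysis keeps everyone randomised and scores those without an outcome as failures. Recruiting 100 to retain 70 restores the number of completers, but it does not undo the dilution of the remission rates once the missing participants return to the denominator.

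At stake is the main justification for the final sample size on the primary outcome. A reader takes it to mean a 10% chance of missing a true effect of the stated size, and the planned analysis may not deliver that.

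**Working it through.** **Inputs from the protocol.** 100 randomised 1:1, so 50 per arm; 70 completers, so 35 per arm; rates 35% and 5%; significance level 0.05; missing counted as non-remission. **Assumed:** two-sided testing; where loss matters, 30% in each arm, with no 24-week outcome for those lost.

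**Step 1: reproduce the stated 90%.** Pooled normal approximation without continuity correction, mean rate 0.20:

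z = [0.30 × √35 − 1.960 × √(2 × 0.20 × 0.80)] / √(0.35 × 0.65 + 0.05 × 0.95)
= (1.7748 − 1.1087) / 0.5244 = 1.270, so power = Φ(1.270) = 89.8%.

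This matches the stated figure.

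**Step 2: the named test on the same inputs.** Power is the sum, over all pairs of remission counts, of the two binomial probabilities multiplied together wherever the two-sided Fisher p-value is at most 0.05.

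| Per arm | Rates | Fisher power |
|---|---|---|
| 35 | 35% vs 5% | 87.1% |
| 37 | 35% vs 5% | 89.5% |
| 38 | 35% vs 5% | 90.6% |

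A simulated stratified exact test (four country-by-sex strata, even sex split assumed, 20,000 runs) gives 87.4% at 35 per arm, so stratification does not recover 90%.

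**Step 3: compare the two calculations.** The usual sample-size formula for two proportions at 90% power gives:

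| Rates | Uncorrected, per arm | Continuity-corrected, per arm |
|---|---|---|
| 45% vs 5% | 23 | 28 |
| 35% vs 5% | 36 | 42 |

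The initial 28 per arm matches the corrected column (exact Fisher power there is 93.3%). The later 35 per arm lies close to the uncorrected column and well short of 42. The two figures therefore do not appear to come from the same method.

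**Step 4: apply the missing-outcome rule.** The protocol does not say whom the rates describe, so both readings are shown.

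- *Completer rates.* 0.70 × 35% = 24.5% and 0.70 × 5% = 3.5%, in 50 per arm. Fisher power is 82.9% (stratified, by simulation, 83.2%).
- *All-randomised rates.* 35% vs 5% in 50 per arm. Fisher power is 96.8%.

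**Step 5: what gives 90% on the completer reading.** With 39% among completers, 0.70 × 39% = 27.3%. Against 3.5% in 50 per arm, Fisher power is 90.3%.

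**The case against.** **The test is not firmly fixed.** The sentence with the 90% names none, Pearson's test is left open, and sidedness is unstated. This is fair, and it is why two-sided Fisher is stated here as an assumption. It does not rescue the figure: at 35 per arm one-sided Fisher at 0.05 gives 92.5% and exact Pearson power is 92.6%. Pearson would give 91.2% on the diluted rates, but the authors' own expectation of very few control remissions points to Fisher.

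**The rates may be meant for all randomised participants.** This stands as a possibility. Power is then 96.8% and the stated 90% is conservative. The completer reading is more natural because the sample size is set to completers, but it is not stated, so 83% is a conditional result.

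**The practical effect is small.** The test discrepancy alone is 2.9 points and disappears if the control rate is 4% (90.7%), the DiRECT control rate that the section cites; 5% is given as an upper bound. At the initial planning rates of 45% vs 5% among completers, the diluted comparison (31.5% vs 3.5%, 50 per arm) still has 96.4% power. This stands and limits the severity.

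**A stronger reading is not supported.** A reader might infer that drop-out lowers only the intervention rate, giving 24.5% vs 5% in 50 per arm, power near 73% and a type II error as high as 27%. The documents do not support that. Missing controls are also scored as non-remission. Holding control remission at 5% of all 50 (2.5 participants) would need either no control loss, hence 35 + 50 = 85 completers rather than 70, or 2.5/35 = 7.1% remission among completing controls, above the stated ceiling of 5%.

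**Conclusion.** The point holds in two parts.

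- **Test.** For 35 per arm and 35% vs 5%, the stated 90% matches a normal approximation. The Fisher test that the protocol names and expects to use has 87.1% power, assuming two-sided 0.05.
- **Population.** The figure describes an analysis of completers that is not the planned primary analysis. Under the missing-outcome rule, power is about 83% if the rates are completer rates with 30% missing in each arm, a type II error of about 17% instead of 10%. It is about 97% if they are all-randomised rates.

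It does not follow that the trial is underpowered: that depends on a definition the text does not give, and on a control rate stated only as a ceiling. This is an error in a reported figure together with an ambiguity. It should be corrected, but it does not call the design into question.

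**What to change.** Revise the expanded-sample paragraph in the Sample size section so that it:

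1. names the test and states its sidedness;
2. says whether 35% and 5% are rates among completers or among all randomised;
3. gives power for the analysis that will be run, meaning 50 per arm with missing outcomes counted as non-remission.

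If completer rates are meant, suitable text would be: *With 50 per arm and 30% in each arm missing and counted as non-remission, a two-sided Fisher's exact test at 0.05 has about 83% power if remission among completers is 35% vs 5%; 90% power requires about 39% among intervention completers.* If all-randomised rates are meant, the figure for 35% vs 5% is about 97%.

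The cost is a text change only. Recruitment, follow-up and the analysis are unaffected. On the completer reading, the reported power becomes less favourable.

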### Statistical analyses

Our primary outcome measures the proportion of remission in the intervention arm relative to the control arm. We will apply intention-to-treat principles for the primary outcome, assuming that remission of diabetes did not occur if information is not available. Based on the DiRECT and DIADEM-I trials, we estimate that remission counts in the control arm could be less than 2. We will therefore use stratified Fisher’s exact test statistics (ie, stratification by country and by sex) if remission counts are low in the control arm but consider Pearson χ^2^ test, if appropriate. If numbers permit, logistic ORs with 95% CIs (exact method) will also be performed to further quantify the efficacy of intervention over the control group, after adjusting for factors used to stratify the randomisation (country, age or sex); we will not have missing values for these covariates. Subgroup analyses for the primary outcome will be performed by country, sex and the degree of weight loss (<5%, 5%–10%, 10%–15%, >15% as examined in the DiRECT trial,^9^ collapsing categories as needed, and by exercise adherence (<50%, >50% of supervised sessions attended). In a per-protocol analysis, we will restrict the intervention group to those who achieved at least 10% wt loss and adhered to at least two thirds of prescribed exercise sessions.

We will analyse dichotomous secondary outcomes (eg, diabetes remission at 12 weeks, hypertension remission at 12 and 24 weeks) as described for the primary outcome. We will analyse continuous key secondary outcomes (eg, left ventricular peak early diastolic strain rate, lean soft tissue mass) through linear regression or log-linear regression, as appropriate, with stratification by country and sex.

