### Aims

Among adults 18–45 years of age with obesity, within 6 years of a T2DM diagnosis, and not on insulin therapy, we will quantify the remission efficacy of a 12-week low energy diet combined with supervised exercise, followed by a 12-week phase of weight and exercise maintenance. We define T2DM remission as a haemoglobin A1c (HbA1c) value less than 6.5% (48 mmol/mol) at 24 weeks, without use of antihyperglycaemic medications during the prior 12 weeks, concordant with the international consensus definition.^3–6^

Through comprehensive cardiovascular MR (CMR), we are also assessing circumferential peak early diastolic strain rate, a sensitive measure^22^ with excellent test–retest reproducibility^28^; end-diastolic mass to volume ratio, a marker of concentric left ventricular remodelling^29^; and measures of aortic distensibility, a key determinant of concentric remodelling in T2DM.^29^ We will also ascertain impacts on a range of other measures (table 1) of insulin resistance, fitness, adiposity, cardiorenal parameters, diet, physical activity, mood and quality of life. We will evaluate participant perspectives (online supplemental appendix 1). Our results will guide the design of a longer-term effectiveness trial.

10.1136/bmjopen-2022-063888.supp1Supplementary data

**Table 1 T1:** Outcomes

	Week 12	Week 24
Primary outcome		
Diabetes remission at 24 weeks		X
Key secondary outcomes		
Other remission, glycaemic and insulin resistance measures		
Diabetes remission at 12 weeks	X	
Haemoglobin A1c, fasting glucose and insulin, Homeostatic Model Assessment for Insulin Resistance	X	X
Main CMR measures		
Left ventricular peak early diastolic strain rate (circumferential and longitudinal, MRI)		X
End-diastolic mass to volume ratio		X
Main fitness measure		
VO_2_ peak	X	X
Main fat and lean mass measures		
Total fat and lean soft tissue mass (DXA)	X	X
Weight and BMI	X	X
Cardiometabolic indicators		
Hypertension remission, systolic and diastolic blood pressure, heart rate	X	X
Total cholesterol, HDL, LDL, triglycerides	X	X
Other secondary outcomes		
Renal function measures		
Creatinine and estimated glomerular filtration rate	X	X
Urine albumin to creatinine ratio	X	X
Hepatic function measures		
Includes alanine aminotransferase (ALT) and bilirubin	X	X
Depression, anxiety and distress		
Hospital Anxiety and Depression Scale and Diabetes Distress Scale	X	X
Indirect calorimetry		
Resting metabolic rate	X	X
Additional cardiac and aortic MRI-based measures		

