### Randomisation and allocation concealment

We randomise participants individually, stratified by country and sex, in blocks of variable size. An independent statistician developed the randomisation sequences uploaded into the Research Electronic Data Capture (REDCap) system. A researcher blinded to the sequence unveils group allocation through an autogenerated randomisation button on REDCap.

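### The adjusted odds ratio lists age as a randomisation factor although it is not one, and it is the only effect estimate with a confidence interval, reported conditionally where control remissions may be very few

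*Protocol article*

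**What the plan says.** All quotes are from the protocol article.

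- **Randomisation and allocation concealment:** "We randomise participants individually, stratified by country and sex, in blocks of variable size". Age is not mentioned.
- **Statistical analyses, primary test:** Fisher's exact test with "stratification by country and by sex".
- **Statistical analyses, continuous key secondary outcomes:** linear or log-linear regression "with stratification by country and sex".
- **Statistical analyses, effect estimate for remission:** "If numbers permit, logistic ORs with 95% CIs (exact method) will also be performed to further quantify the efficacy", and this is to be done "after adjusting for factors used to stratify the randomisation (country, age or sex").
- **Statistical analyses, expected counts:** "we estimate that remission counts in the control arm could be less than 2".
- **Aims:** "we will quantify the remission efficacy".

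The Statistical analyses section opens by describing the remission proportion in one arm relative to the other, but it attaches no estimator or interval to that contrast. Participants without outcome information are counted as not in remission.

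**The concern.** There are two separate problems in one sentence.

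The first is factual. The sentence describes its covariates as the randomisation factors and then lists one that is not. An analyst who follows the list adjusts for age. One who follows the description does not. The word joining the last two items also leaves unclear whether all the listed factors enter the model. Age may matter for the method too. The interval is to be exact, and if age entered as a continuous covariate (its form is not stated), conditioning on it could leave very few alternative arrangements of the data to work with.

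The second concerns what will be estimated. The aim is to quantify efficacy, and the only quantity with an interval is an odds ratio whose reporting depends on the counts, with no threshold given. An odds ratio is least informative when one arm has almost no events, and the plan itself names that situation as possible. The decision to report the interval would then be taken after the counts are seen, and the interval might have no upper limit or one in the hundreds.

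**Working it through.** **1. Stratification factors.** The randomisation section, the primary test and the continuous outcomes all use country and sex. Only the odds-ratio sentence adds age. No arithmetic is needed: three statements agree and one does not.

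**2. The plan's own figures.** The Sample size section cites 46% against 4% remission with an odds ratio of 19.7. From the rounded percentages, (0.46/0.54)/(0.04/0.96) = 20.4. Rounding alone allows (0.455/0.545)/(0.045/0.955) = 17.7 to (0.465/0.535)/(0.035/0.965) = 24.0, so 19.7 is consistent. The first design (45% against 5%, 90% power, 28 per arm) also reproduces: the continuity-corrected two-proportion formula gives 28 per arm, and 56/0.70 = 80 recruited. Nothing below alters these numbers.

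**3. Chance of very few control remissions.** Inputs: 100 randomised 1:1, so about 50 controls; control rate up to 5%; 30% drop-out allowance; missing counted as non-remission. If missingness is unrelated to remission (an assumption), 5% becomes 0.05 × 0.70 = 3.5%. The formulas are P(0) = (1 − p)^50 and P(0 or 1) = (1 − p)^50 + 50p(1 − p)^49.

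| Control rate | P(0) | P(0 or 1) |
|---|---|---|
| 5% (design ceiling) | 0.077 | 0.279 |
| 4% (cited trial's control arm) | 0.130 | 0.400 |
| 3.5% (5% with 30% missing) | 0.168 | 0.474 |

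**4. What the exact odds ratio gives.** Given the total number of remissions s in a two-by-two table, P(X = k) is proportional to C(50, k) · C(50, s − k) · ψ^k, where X is the intervention count and ψ the odds ratio. The limits are the values of ψ that put 0.025 in each tail. With no control remissions, the observed X equals s, the largest possible value. P(X ≤ s) is then 1 for every ψ, so no upper limit exists, and the likelihood rises without a maximum. The lower limit still exists.

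The intervention counts are assumptions: 18/50 is close to the 35% design rate (0.35 × 50 = 17.5), and 12/50 is close to that rate with 30% missing (0.35 × 0.70 × 50 = 12.25). The risk difference uses the Newcombe interval. All entries are unstratified.

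| Intervention | Control | Exact OR (95% CI) | Risk difference (95% CI) |
|---|---|---|---|
| 18/50 | 0/50 | not finite (6.2 to ∞) | 0.36 (0.22 to 0.50) |
| 18/50 | 1/50 | 26.8 (3.9 to 1171) | 0.34 (0.19 to 0.48) |
| 18/50 | 2/50 | 13.2 (2.85 to 125) | 0.32 (0.17 to 0.46) |
| 12/50 | 0/50 | not finite (3.3 to ∞) | 0.24 (0.12 to 0.37) |
| 12/50 | 1/50 | 15.1 (2.1 to 675) | 0.22 (0.09 to 0.36) |
| 12/50 | 2/50 | 7.4 (1.5 to 72) | 0.20 (0.06 to 0.34) |

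First row by hand: the Wilson limits are 0.241 and 0.499 for 18/50, and 0 and 0.071 for 0/50. The lower limit is 0.36 − √(0.119² + 0.071²) = 0.22. The upper limit is 0.36 + 0.139 = 0.50.

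**5. With strata.** Take 20 UK and 30 Canadian participants per arm and assume an equal sex split. The strata then hold 10, 10, 15 and 15 per arm. Let the 18 intervention remissions fall 4, 3, 6 and 5. The exact common odds ratio is:

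- 0 control remissions: no finite conditional estimate, 95% CI 5.8 to ∞, median-unbiased estimate 35.
- 1 (in a Canadian stratum): 25.4 (3.7 to 1103).
- 2 (one in each country): 12.6 (2.8 to 119).

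The Mantel-Haenszel risk difference has weights 5, 5, 7.5 and 7.5. With no control remissions it is (5 × 4/10 + 5 × 3/10 + 7.5 × 6/15 + 7.5 × 5/15)/25 = 9/25 = 0.36. With 1 and 2 control remissions it is 8.5/25 = 0.34 and 8/25 = 0.32, the same as unstratified. The stratified interval was not computed.

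**The case against.** The strongest reply is that little depends on this sentence. The odds ratio is supplementary, the primary test and the continuous outcomes name the right strata, and the phrase about randomisation factors, read with the randomisation section, already points to country and sex. That limits the consequence, but the list still contradicts the rule it is meant to illustrate.

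A reader might infer more than the text supports:

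- *That the odds ratio fails near zero control remissions.* The plan specifies the exact method. At zero it still yields a valid lower limit and can yield a median-unbiased estimate. At 1 or 2 the limits are finite, though very wide.
- *That the plan expects fewer than 2 control remissions.* It says the count could be that low. At the 5% ceiling, 2.5 are expected among 50, and an unbounded interval would arise in roughly 8% to 17% of trials, so usually not.
- *That the trial may end with no usable effect size.* Nothing suggests that the arm proportions will be withheld, and a difference can be read from them.
- *That an odds ratio is the wrong measure.* It is a standard one, and the article cites an odds ratio from an earlier remission trial. It misleads only if it is read as a risk ratio, which the article does not do.

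It is also fair to say that a condensed article may leave an interval method to the full protocol or analysis plan. That answers a complaint about missing detail. It does not answer the point that the one interval the article does fix depends on counts which the same section says may be too few.

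**Conclusion.** Both parts hold in limited form. Naming age as a stratification factor is a plain internal contradiction, confined to the adjusted odds ratio. The effect measure is poorly matched to the counts the plan allows for. There is about an 8% chance (5% rate, 50 controls) to 17% chance (30% missing as non-remission) of an estimate with no upper limit. The chance of 0 or 1 control remission is 28% to 47%, and for 1 remission the upper limit runs to several hundred or more on the assumed intervention counts. On the same counts, one more control remission moves the risk difference by 2 points and its interval stays finite.

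The probabilities rest on the control rate and on missingness being unrelated to remission. The intervals rest on the illustrative intervention counts and, except where strata are stated, on unstratified tables. The validity of the primary test is not in question.

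**What to change.** 1. In the odds-ratio sentence, name country and sex as the adjustment factors, both included. If age is wanted, list it separately as a baseline covariate that is not a stratification factor, and state its form.
2. State that the risk difference in remission with a 95% CI, stratified by country and sex, is always reported with the primary test, whatever the counts. Mantel-Haenszel weights with a stratified score or Newcombe-type interval would serve, because they do not collapse when an arm has no events.
3. Keep the exact odds ratio as supportive and remove the condition on its reporting. If the upper limit is infinite, report it as such.

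The dichotomous secondary outcomes are to be analysed as described for the primary outcome, so the same wording would cover them. The cost is a few lines of text and a small amount of extra analysis code. The primary test, the sample size and trial conduct stay as they are.
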